#### Secondary endpoint

For each endpoint (points 1-6 provided below), we will perform the same analysis as the primary endpoint at each evaluation time point after starting treatment from baseline.Change in upper limb BRS at weeks 2 and 4,Amount of change in Functional Independence Measure (FIM) at weeks 2 and 4,Change in upper limb FMA at weeks 1, 3, and 4,Amount of change in BI at weeks 2 and 4,Amount of change in grip strength at 1, 2, 3, and 4 weeksUpper limb manual muscle strength test: the amount of change in manual muscle test (MMT) at weeks 1, 2, 3, and 4.

For implementation compliance, the treatment implementation status for each day will be aggregated.

The BRS classifies the recovery process into six stages. This classification, established from clinical observations of many hemiplegic patients, is based on the degree of spasticity, synergy, and voluntary movement. A previous study reported that this classification of BRS has face validity, but it has never been assessed for reliability and validity [18]. In clinical practice, BRS is used for simple evaluation of motor paralysis, but FMA is used for more detailed evaluations. FMA is rated higher than BRS for its validity and reliability. Therefore, for the purpose of this study, we will be using both outcome measures.

The BI, which is used as a simple and useful evaluation of a patient’s independence, can be accurately and quickly scored by adhering to the definition of 10 items concerning ADL, with a score range of 0–100. The FIM is considered more valid than BI and equally reliable in the assessment of disability [19]. The FIM was developed for precise evaluation of ADL [20] and is divided into two sections: a motor section, which includes 13 items, and a cognitive section, which includes 5 items. Each item is graded from 1 (totally dependent) to 7 (completely independent), and the total FIM score range is 18–126. BI scores have been closely correlated with FIM [21]. Both will be used in this study because of the limitations of using only one assessment of ADL.

### Sample size

Since this is an exploratory study, the target number of cases is set at 20 from the feasibility viewpoint. At this time, if the average ± SD of the change amount of the main endpoint upper-limb FMA is estimated to be 6.0 ± 2.0, with reference to a previous report [22], the width of the 95% confidence interval of the change amount is approximately 1.9. As the amount of change in the case of normal treatment is expected to be 3.0 ± 1.0, it is considered that the effect of this treatment can be sufficiently confirmed.

### Statistical analysis

#### Characteristics of background and baseline values

Summary statistics (number of cases, mean, standard deviation, minimum, median, and maximum) will be reported for background and baseline distributions and continuous values in FAS, and frequency and percentage will be recorded for discrete values.

#### Statistical analysis plane

The primary endpoint is the change in the amount of upper-limb FMA from baseline to week 2. For efficacy evaluation, the full analysis set (FAS) and per-protocol set (PPS) will be used. The FAS is defined as the patient population excluded from the SS for any of the following reasons: ineligible cases after enrolment and cases with no data related to efficacy at any time after the start of study treatment. The PPS is defined as the patient population excluded from the FAS for any of the following reasons: violation of safety-related exclusion criteria, met criteria for study discontinuation, violation of effectiveness-related inclusion criteria, use of prohibited treatment, study rehabilitation compliance rate < 70%, or treatment period < 1 week.

Concerning the primary and secondary endpoints, the degree of improvement in parameters before and after intervention will be compared using the paired *t* test with a significance level of 0.05 and a tendency level of 0.10, and the improvement will be estimated using 95% CI. If the improvement in FMA between before and after the intervention is ≤ 0.10, we will proceed to the next pivotal clinical trial. Similarly, we will consider progression to the next trial if the BRS, FIM, grip strength, and BI values are ≤ 0.10. Missing values in the efficacy analysis will be supplemented with the immediately preceding value (last observation carried forward). We will analyze covariance with the intervention value as a covariate, and calculations will be performed using Statistical Package for the Social Sciences 22.0J (SPSS Japan, Tokyo, Japan).

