## Key messages regarding feasibility

The protocol rehabilitation therapy in this study is a new method of handy portable low-frequency treatment device, integrated volitional control electrical stimulation (IVES+), that placed the stimulating electrodes in antagonistic muscles.The enrolment for the patients defined as upper limb Brunnstrom stage (BRS) of 2–4 is critical to evaluating the efficacy of this study.This study will explore the usefulness of IVES+ in recovery from motor paralysis to cancel synkinesis in patients with cerebrovascular disorders.The duration of hospitalization for rehabilitation is limited, and long-term efficacy is difficult to evaluate.

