**Fig. 1 Fig1:**
[figure not shown]
Study design. Twenty patients with incomplete paralysis and cerebrovascular disorders participated in this study. After confirmation of eligibility, the enrolled patients will be assigned to the study rehabilitation using IVES+. MMSE, Mini-Mental State Examination; BRS, Brunnstrom stage; FMA, Fugl-Meyer Assessment; FIM, Functional Independence Measure; BI, Barthel Index; MMT, manual muscle test, Adverse event; AE

**Table 1 Tab1:** Inclusion, exclusion, and discontinuation criteria

Inclusion criteria	
1. Within 1 month of a cerebrovascular event (cerebral infarction, cerebral hemorrhage, subarachnoid hemorrhage).	
2. With upper limb Brunnstrom stage (BRS) 2–4.	
3. Aged 20 years or older at the time of obtaining informed consent.	
4. Provides written informed consent to participate in this clinical study.	
Exclusion criteria	
1. Received treatments, such as botulinum therapy, repeated transcranial magnetic stimulation, and transcranial direct current stimulation, within 90 days of obtaining consent.	
2. With a history of surgery (including device therapy) or intravenous t-PA for a cerebrovascular event (cerebral infarction, cerebral hemorrhage, subarachnoid hemorrhage).	
3. Cognitive decline (Mini-Mental State Examination (MMSE) is 21 or less).	
4. Severe skin symptoms on the affected upper limb.	
5. Have a history of epileptic seizures.	
6. With a history of substance abuse or addiction (including alcoholism) at the time of enrolment and within the past year, or patients with complications.	
7. Using an implantable cardiac stimulator, such as a cardiac pacemaker or an implantable assisted heart.	
8. Using deep brain stimulation.	
9. With metal (excluding titanium products) implanted in the affected upper limb.	
10. Who are pregnant or may become pregnant. 11. Who are judged by doctors to be inappropriate as research subjects.	
Discontinuation criteria	
1. There was an offer to decline study participation or withdraw consent.	
2. Who were found not to meet eligibility after enrolment.	
3. The primary disease was completely cured and continued use was no longer necessary.	
4. The device therapy used in this study was judged unfavorable due to exacerbation of the primary disease.	
5. It is difficult to continue the study due to exacerbation of complications.	
6. It is difficult to continue the study due to illness.	

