7. Although the frequency of use has been reduced according to the protocol, it is difficult to use even if the lower limit (less than 70% of the total planned number of uses) is reached.	
8. Who became pregnant.	
9. Poor compliance (if it is judged that less than 70% of the total planned number of uses will be used).	
10. Who cannot receive intervention due to hospital transfer.	
11. The entire study was discontinued	
12. For other reasons, the doctor judged it appropriate to discontinue the study.

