### Endpoints

#### Primary endpoint

The primary endpoint is the mean and standard deviation (SD) for changes from baseline in the upper limb FMA at week 2. In addition, the effectiveness of this treatment will be examined by comparing the calculated mean value with 3.0, which is estimated as the amount of change in the case of conventional treatment. The FMA scale was developed as the first quantitative evaluative instrument for measuring sensorimotor stroke recovery in patients with hemiplegic stroke. The FMA is an efficient clinical examination method that has been widely tested in stroke populations. Its primary value is the 66-point motor domain, which has received the most extensive evaluation of upper-limb function [14]. The change in the FMA score can be used to evaluate the degree of cancelation of synkinesis. FMA has the advantage of being able to capture the patient’s overall picture and making it easier to predict the effects of rehabilitation [15, 16]. FMA has been reported to correlate with the degree of independence in activities of daily living [17]. In Japanese hospitals, the general length of stay in an acute care hospital is around 2 weeks; therefore, the timing of the endpoint was planned. We planned to conduct a subgroup analysis to adjust for the number of trials after this study.

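### The per-protocol set for the week-2 primary endpoint can lose patients because of events in weeks 3 and 4

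*Protocol article*

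**What the plan says.** The protocol article (Primary endpoint; Statistical analysis plane) sets the primary endpoint as the change in upper-limb FMA from baseline to week 2. The Intervention section plans one session a day, 5 days a week, for 4 weeks, or about 20 sessions.

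Efficacy is to be evaluated in both the FAS and the PPS, and the article does not say which leads. The PPS is the FAS minus patients with any of several listed reasons. Among these are "met criteria for study discontinuation, violation of effectiveness-related inclusion criteria, use of prohibited treatment, study rehabilitation compliance rate < 70" per cent. The discontinuation and prohibited-treatment items have no time window, and the compliance item does not state its denominator.

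Table 1 lists the discontinuation criteria. Three matter here, and none has a time window:

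- Criterion 3: "The primary disease was completely cured and continued use was no longer necessary".
- Criterion 4: "The device therapy used in this study was judged unfavorable due to exacerbation of the primary disease".
- Criterion 10: "Who cannot receive intervention due to hospital transfer".

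On the choice of week 2, the Primary endpoint section explains that "the general length of stay in an acute care hospital is around 2 weeks; therefore, the timing of the endpoint was planned".

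**The concern.** A per-protocol analysis of an endpoint should contain the patients who followed the protocol up to the time that endpoint was measured. The rule as written asks for more. A patient must also avoid every discontinuation criterion during the 2 weeks after the primary measurement.

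Two of the criteria, cure and worsening, are themselves disease outcomes. Removing a patient from the week-2 analysis because of one of them is selection on a later outcome. The third, transfer, is an event the protocol itself anticipates: week 2 was chosen with the usual length of an acute stay in mind, and transfer has its own discontinuation criterion. The endpoint was placed with departures in view, but the PPS rule removes patients for departing after it.

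What is at stake is the interpretation of one of the two efficacy analyses. If PPS and FAS results differed, a reader could not tell whether this reflected adherence up to week 2 or events after it.

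**Working it through.** **Inputs**

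- Schedule: 5 sessions a week for 4 weeks (Intervention).
- Primary assessment: week 2 (Primary endpoint).
- PPS compliance limit: 70% (Statistical analysis plane).
- Target sample 20; expected change 6.0 with SD 2.0; reference change 3.0 (Sample size).

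**The plan's own figure.** Width of the 95% confidence interval = 2 × t(0.975; 19) × SD/√n = 2 × 2.093 × 2.0/√20 = 1.87. This agrees with the stated value of about 1.9.

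**Following one patient through the rule**

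1. Total planned uses: 5 × 4 = 20. Uses scheduled by week 2: 5 × 2 = 10.
2. Suppose the patient receives all 10, has a valid week-2 FMA, and is transferred early in week 3 so that treatment stops.
3. FAS: the patient is eligible and has efficacy data after the start of treatment, so stays in with the observed week-2 value. Nothing needs to be carried forward for week 2.
4. PPS, discontinuation item: criterion 10 is met, so the patient is out. Cure (criterion 3) or worsening (criterion 4) in weeks 3 or 4 gives the same result.
5. PPS, compliance item: counted over the full course, 10/20 = 50%, below the limit of 0.70 × 20 = 14 uses. Counted to week 2, 10/10 = 100%, above the limit of 0.70 × 10 = 7 uses. The answer depends on the unstated denominator, but step 4 alone is enough to exclude the patient.

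**Size.** Each affected patient is 1/20 = 5% of the target sample. The article gives no exit rate, so the PPS sizes below are assumptions. They use SD 2.0 and a true change of 6.0, tested against 3.0 with a two-sided 5% t test (noncentrality 3.0/(2.0/√n)).

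| Patients in PPS | 95% CI width | Power |
|---|---|---|
| 20 | 1.87 | 1.000 |
| 18 | 1.99 | 1.000 |
| 16 | 2.13 | 1.000 |
| 14 | 2.31 | 0.999 |
| 12 | 2.54 | 0.997 |
| 10 | 2.86 | 0.987 |

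Loss of power is not the issue under the plan's assumptions.

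**Selection.** Removing one patient whose change lies d points from a mean of 20 moves that mean by d/19. For d = 4 (two SDs) this is 4/19 = 0.21 points. As an outer illustration, removing exactly the lowest 20% of normally distributed changes would raise the mean from 6.0 to about 6.7, and removing the highest 20% would lower it to about 5.3. Nothing in the article suggests selection that sharp. These exits are triggered after week 2, and the patients concerned need not have extreme week-2 changes.

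**The case against.** The strongest reply has three parts.

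- **A single PPS for the whole regimen is a recognised choice.** It keeps one population across weeks 1 to 4, and visit-specific rules are often left to the full protocol or analysis plan. This holds for missing detail, but the article states an itemised rule, and following that rule gives the result shown. A full-course set suits a week-4 endpoint better than a primary endpoint halfway through the course.
- **The FAS is unaffected, so a reader can compare the two sets.** This stands, and it limits the point to a minor one.
- **No decision is shown to change.** The progression rule is not tied to the PPS, the Discussion names feasibility and safety as the main objectives, and a single-arm study has no arms to unbalance. This also stands.

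A reader might infer more than the article supports:

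- **Criterion 9.** It reads "Poor compliance (if it is judged that less than 70% of the total planned number of uses will be used"), which could be taken to classify every early departure as poor compliance. The label and the separate transfer criterion point the other way, and the point does not need it.
- **The minimum treatment period.** The exclusion "or treatment period < 1 week" might suggest that everyone treated for longer was meant to stay. The exclusions are alternatives, so a floor under one says nothing about the others.
- **Frequent late exits.** The statement that "The duration of hospitalization for rehabilitation is limited, and long-term efficacy is difficult to evaluate" concerns long-term follow-up. The usual acute stay is a general figure, and patients may enrol up to 1 month after onset. Neither gives an exit rate for weeks 3 and 4.
- **A bias of known direction.** Removing late recoverers and removing late decliners could pull the mean in opposite directions, and transfer has no evident direction.

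**Conclusion.** The point holds as a minor design weakness. As written, membership of the PPS for the week-2 primary endpoint depends partly on cure, worsening or transfer in weeks 3 and 4, after the endpoint has been measured. A patient with all 10 scheduled uses and a valid week-2 FMA can be excluded.

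This rests on reading the PPS definition and Table 1 literally, since neither has a time window, and on 10 uses being scheduled by week 2, which follows from the stated weekly schedule. It does not depend on the compliance denominator. The effect is limited to the PPS. How many patients would be affected, and in which direction the PPS mean would move, cannot be determined from the article.

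**What to change.** For the primary week-2 analysis, apply the PPS exclusions for discontinuation, prohibited treatment and compliance only to events up to the week-2 assessment. Count compliance over the 10 uses scheduled by then, with at least 7 required.

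For the other time points there are two options. Either apply the same principle throughout, so that membership at each assessment rests on events and scheduled uses up to that assessment, including weeks 1 and 3; or keep the full-course PPS (at least 14 of 20 uses) for week 4 only and state which set serves weeks 1 and 3.

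The cost is a wording change to the PPS definition. No new data are needed, because treatment status is already to be recorded and aggregated by day (Secondary endpoint). Table 1 does not have to change. The drawback is that PPS membership differs between time points, so the number of patients and the reasons for exclusion must be reported for each.

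### The FMA progression rule tests for any change from baseline and ignores the 3.0-point gain the plan expects under conventional treatment, so a device with no effect would almost certainly progress

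*Protocol article*

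**What the plan says.** Four parts of the protocol article bear on this point.

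- **Statistical analysis plane, test.** For the primary and secondary endpoints, "the degree of improvement in parameters before and after intervention will be compared using the paired" t test, at a significance level of 0.05 and a tendency level of 0.10, with a 95% CI for the improvement.
- **Statistical analysis plane, progression.** "If the improvement in FMA between before and after the intervention is ≤ 0.10, we will proceed to the next pivotal clinical trial". A second rule says progression will likewise be considered on values of 0.10 or less for BRS, FIM, grip strength and BI. Neither rule mentions 3.0.
- **Primary endpoint.** As an addition to the mean and SD of the week-2 change, effectiveness is to be examined by "comparing the calculated mean value with 3.0, which is estimated as the amount of change in the case of conventional treatment". No test, level or link to progression is given.
- **Sample size.** "the target number of cases is set at 20 from the feasibility viewpoint"; "the change amount of the main endpoint upper-limb FMA is estimated to be 6.0 ± 2.0"; "the width of the 95% confidence interval of the change amount is approximately 1.9"; and, for comparison, "the amount of change in the case of normal treatment is expected to be 3.0 ± 1.0". From this the section concludes that the treatment effect can be adequately confirmed.

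The Design section adds that the device is given together with regular rehabilitation, and Table 1 limits entry to patients within 1 month of the event.

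**The concern.** A before-after test in a single arm asks whether patients changed at all. These patients are in early recovery and receive regular rehabilitation, and the plan itself expects them to gain 3.0 points without the device. Zero change is therefore a null the plan already expects to be false when the device does nothing. Rejecting it shows recovery, and says nothing about what the device adds.

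At stake is the decision to launch a pivotal trial. The plan holds the benchmark that would make the decision informative, but the progression rule does not use it.

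**Working it through.** **Inputs.** From Sample size: n = 20; change with the device 6.0 ± 2.0; change under normal treatment 3.0 ± 1.0. From Statistical analysis plane: paired t test, cut-off 0.10.

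**Readings I had to make.** The rule literally says the improvement is at most 0.10. I read 0.10 as a p-value, because the preceding sentence sets 0.10 as the tendency level. I take the test as two-sided and the time point as week 2, that of the primary endpoint. SDs above 2.0 and true means other than 3.0 and 6.0 are my assumptions.

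**Step 1: reproduce the plan's own figure.** 95% CI width = 2 × t(0.975, 19) × SD/√n = 2 × 2.093 × 2.0/√20 = 1.87. This agrees with the stated width of about 1.9.

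**Step 2: smallest observed mean that passes the rule as written.** t(0.95, 19) × SD/√n = 1.729 × 2.0/√20 = 0.77 points at SD 2.0. That is about a quarter of the gain expected without the device (0.77/3.0 = 0.26).

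**Step 3: probability of progressing when the device adds nothing.** The true mean change is 3.0 and the null is 0. Under a noncentral t with 19 df, the noncentrality is 3.0/(SD/√20), and the probability is the upper tail beyond 1.729.

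| SD | Source of SD | Noncentrality | P(progress) |
|---|---|---|---|
| 1.0 | plan, normal treatment | 13.4 | >99.99% |
| 2.0 | plan, with device | 6.7 | >99.99% |
| 3 | assumed | 4.5 | 99.6% |
| 4 | assumed | 3.4 | 94% |
| 5 | assumed | 2.7 | 83% |
| 6 | assumed | 2.2 | 70% |

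Simulating 200,000 trials at each of SD 1.0 and 2.0 gave 100% to the precision of the simulation. Using the 0.05 level instead changes little at the plan's SDs (99.999% at SD 2.0).

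**Step 4: the same test against 3.0.** The observed mean needed at SD 2.0 is 3.0 + 0.77 = 3.77. A device that adds nothing passes in the favourable direction 5% of the time, by construction (simulated: 5.1% at SD 1.0, 5.0% at SD 2.0). At 6.0 ± 2.0 the noncentrality is (6.0 − 3.0)/(2.0/√20) = 6.7 and power exceeds 99.99%.

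**Step 5: where the repaired rule is weaker (SD 2.0, assumed means).**

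- If the true mean with the device is 4.0, the noncentrality is 1.0/(2.0/√20) = 2.24 and power is about 70%.
- If conventional care really yields 3.5, a device that adds nothing passes with noncentrality 0.5/(2.0/√20) = 1.12, about 29% of the time.
- If conventional care yields 4.0, it passes about 70% of the time.

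**The case against.** The strongest reply is that the benchmark is already in the plan. The Primary endpoint section compares the mean with 3.0, and the analysis section provides a 95% CI that anyone can set against it. A reader might infer that the plan states two competing null hypotheses, or that the sample size was computed for a test other than the one to be run. The text supports neither. The comparison with 3.0 is introduced as a supplement and carries no null or level. The Sample size section is a precision statement, and the CI it describes is the one planned. What stands is narrower: the benchmark has no role in the progression decision.

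A second reply is that the study is exploratory. The Discussion names feasibility and safety as the main objectives and concedes the limits of a small, short, single-arm design, and progression leads only to another trial. A reader might go further the other way and infer that the trial's only decision is uninformative. That is too strong, since a second progression rule exists and the planned CI remains interpretable. The exploratory context lowers the consequence, but it does not repair the rule: the stated progression criteria are efficacy p-values, and an exploratory label does not justify a criterion that is met whether or not the device works.

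A third reply is that 3.0 is itself an uncertain fixed figure. That is correct, and it limits what the repaired rule can claim. It does not favour zero, which lies further from the plan's own expectation.

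**Conclusion.** The point holds for the FMA progression rule as written. On the plan's own figures (n = 20, true change 3.0, SD 1.0 or 2.0), a device with no effect would progress with probability above 99.99%. At assumed SDs of 4 and 6 the figure is 94% and 70%, still far above any nominal error rate. The conclusion rests on the p-value, two-sided and week-2 readings declared above.

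The second rule, on BRS, FIM, grip strength and BI, uses the same before-after test and so has the same weakness. Its size cannot be computed, because the article gives no expected conventional change for those measures.

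It would be tempting to say that testing against 3.0 costs nothing and guarantees a 5% error rate. Neither is unconditional: power is near 100% at 6.0 ± 2.0 but not for a smaller benefit, and the 5% holds only if 3.0 is correct.

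**What to change.** In Statistical analysis plane:

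1. Test the mean week-2 change in upper-limb FMA against 3.0, and proceed only if the lower limit of the two-sided 90% CI (matching the plan's 0.10 level) exceeds 3.0. Say explicitly that 0.10 is a two-sided p-value cut-off and that the rule applies at week 2.
2. Keep the before-after paired t test as description.
3. Treat BRS, FIM, grip strength and BI as supportive, and do not let them trigger progression on their own.
4. Give the comparison in the Primary endpoint section the same test and role, so that the sections agree.
5. Report the lower confidence limit as the largest conventional gain that the result would still beat, and limit the claim to that. Under the planning values the lower 90% limit would be 6.0 − 1.729 × 2.0/√20 = 5.23.

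The cost is a change of wording, with no added patients or data if the planning values hold. The price is a higher bar: about 3.77 instead of 0.77 points at SD 2.0. If the device adds only one point (true mean 4.0, SD 2.0), the trial would progress about 70% of the time.

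### The progression rule is misprinted as a limit on improvement; read as a p-value against zero it is met almost surely by the gain expected under normal treatment, and its secondary route is undefined

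*Protocol article*

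**What the plan says.** The rule stands in the protocol article's section on statistical analysis. Before and after values are to be "compared using the paired *t* test with a significance level of 0.05 and a tendency level of 0.10". For the primary endpoint: "If the improvement in FMA between before and after the intervention is ≤ 0.10, we will proceed to the next pivotal clinical trial". For four secondary endpoints: "Similarly, we will consider progression to the next trial if the BRS, FIM, grip strength, and BI values are ≤ 0.10".

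Three other places bear on it.

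- **Primary endpoint** section: the mean week-2 FMA change is to be set against 3.0, the change estimated for conventional treatment.
- **Sample size** section: "the target number of cases is set at 20 from the feasibility viewpoint"; "the change amount of the main endpoint upper-limb FMA is estimated to be 6.0 ± 2.0" under the study treatment; and "As the amount of change in the case of normal treatment is expected to be 3.0 ± 1.0".
- **Secondary endpoint** section: BRS, FIM and BI are assessed at two visits each (weeks 2 and 4) and grip strength at four (weeks 1 to 4). For all secondary endpoints "we will perform the same analysis as the primary endpoint at each evaluation time point after starting treatment from baseline".

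**The concern.** The rule decides whether the device goes on to a pivotal trial, so it should separate a useful treatment from ordinary early recovery. There are three difficulties.

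1. **Wording.** The 0.10 limit is attached to the improvement, and then to the endpoint values. As printed, the rule is reversed.
2. **Comparator.** If 0.10 is a p-value, it comes from a test against zero change. Patients enter within one month of onset, and the article itself expects them to gain under normal treatment. It names 3.0 as the comparator elsewhere but leaves it out of the rule.
3. **Secondary route.** No visit is named, no sign condition is set, and the text does not say whether one endpoint or all four must reach the limit.

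The stake is a decision to proceed that carries almost no information about the device.

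**Working it through.** **Inputs from the article.** n = 20, single arm; FMA change 6.0 (SD 2.0) with study treatment and 3.0 (SD 1.0) with normal treatment; paired t test; tendency level 0.10. Sidedness is not stated; two-sided is assumed, in line with the 95% CI. SDs above 2.0 and all correlations between endpoints are assumptions.

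**Reproducing the article's figure.** The 95% CI width is 2 × t(0.975; 19) × SD/√n = 2 × 2.093 × 2.0/√20 = 1.87, which agrees with the stated value of about 1.9.

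**Literal reading.** An improvement of 0, or a decline, is at most 0.10 and passes. The planned 6.0 exceeds 0.10 and fails.

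**FMA rule as a p-value against zero.** The smallest mean gain that gives p ≤ 0.10 at SD 2.0 is t(0.95; 19) × 2.0/√20 = 1.729 × 0.447 = 0.77 points. If the true mean is 3.0 (no benefit over normal treatment), the noncentrality is 3.0 × √20/SD, and the noncentral t distribution gives:

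| SD of change | Noncentrality | P(p ≤ 0.10) |
|---|---|---|
| 1 | 13.42 | 1.000 |
| 2 | 6.71 | 1.000 |
| 3 | 4.47 | 0.996 |
| 4 | 3.35 | 0.944 |
| 6 | 2.24 | 0.695 |

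**The same test against 3.0.** At a true mean of 3.0, P(p ≤ 0.10) is 10%, of which 5% has a favourable sign. At a true mean of 6.0 and SD 2.0, the distance from 3.0 is again 3.0, so power is above 99.9%. The observed mean needed to pass is 3.0 + 0.77 = 3.77.

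**Secondary route under no change.** The number of endpoint-visit tests is 2 (BRS) + 2 (FIM) + 2 (BI) + 4 (grip) = 10. For independent tests, P(at least one p ≤ 0.10) = 1 − 0.9^10 = 0.651; in the improving direction it is 1 − 0.95^10 = 0.401. Correlated values are from simulation (n = 20, common correlation ρ, 40,000 runs).

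| Reading | ρ = 0 | ρ = 0.5 | ρ = 0.9 |
|---|---|---|---|
| Any one of 10, either direction | 65% | 50% | 24% |
| Any one of 10, improving only | 40% | 25% | 12% |
| All four endpoints, one visit each | 0.01% | 0.5% | 4% |

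**BRS by paired t.** Suppose 3 of 20 patients gain one stage and 17 are unchanged. The mean is 0.15 and the SD 0.366, so t = 0.15/(0.366/√20) = 1.83 and p = 0.083, which meets the limit. The exact sign test on the three changes gives 2 × 0.5³ = 0.25. A signed-rank test by normal approximation also gives 0.083; its exact version gives 0.25.

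**Carrying 3.0 to the secondaries.** The primary analysis includes the comparison with 3.0, so an instruction to repeat it can be taken to include that figure. It is an FMA value. BRS has six stages, so a patient entering at stage 4 can gain at most 2.

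**The case against.** The best defence is that the intended meaning is recoverable: the preceding sentence sets a tendency level of 0.10, so 0.10 must be a p-value. That is fair, and the literal reading is best taken as a drafting slip. It still needs correcting, and the recovered meaning leads straight to the comparator problem.

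A reader might infer more than the text supports in five ways.

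- **Any secondary result below 0.10 forces progression and overrides a failed FMA.** The article commits to proceeding only on FMA; for the others it will merely consider it. Nothing speaks of overriding.
- **The chance of a false signal is several times 0.10.** This needs the any-one reading and modest correlation. The endpoints are joined by *and*, and if all four must pass the rate is 4% or less. The article also reports BI as closely correlated with FIM, and repeated visits of one measure will correlate too.
- **Worsening counts as success.** The test is framed in terms of improvement, which implies a direction. Only a formal sign condition is missing.
- **Natural recovery also meets the secondary limits.** The article gives no expected change under normal treatment for BRS, FIM, BI or grip strength, so this can be shown for FMA only.
- **The secondaries will certainly be tested against 3.0.** Repeating the primary analysis can also mean only the mean, SD and test of change. The wording is open.

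It can also be said that this is an exploratory study of 20 patients, with feasibility and safety as its main objectives. That excuses the lack of multiplicity control for supportive endpoints. It does not excuse a stated go decision that cannot tell the study treatment from normal treatment.

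**Conclusion.** The concern holds in a limited form. The FMA sentence fails on both readings: literally it is reversed, and as a p-value against zero it is met almost surely without any benefit over normal treatment. That second result rests on the article's own mean of 3.0 and n = 20. It is about 1.000 at the article's SDs of 1.0 and 2.0 and weakens only at larger assumed SDs (0.944 at SD 4, 0.695 at SD 6).

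The secondary route is undefined rather than shown to be lax. Its chance rate runs from 4% or less to 65% according to an any/all choice that the text does not make and correlations that it does not give. Under the recovery that the article expects, multiplicity adds almost nothing, because the FMA rule is already met. The missing comparator is therefore the main defect.

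The 5% error rate for the corrected rule holds if the true mean under normal treatment is exactly 3.0.

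**What to change.** 1. Replace the FMA sentence with a rule that names the statistic, visit, comparator and direction. For example: proceed if the week-2 mean FMA change is above 3.0 and the two-sided t test against 3.0 gives p ≤ 0.10. Equivalently, the lower limit of the 90% CI is at or above 3.0.
2. Remove the threshold for BRS, FIM, grip strength and BI, and report them as supportive (mean change with 95% CI). If a threshold is kept, fix the visit, the sign condition and the any/all requirement.
3. State in the secondary endpoint section that the comparison with 3.0 applies to FMA at week 2 only.
4. If BRS is tested, use an exact sign or exact signed-rank test and give the proportion gaining at least one stage. The normal approximation to the signed-rank test would not cure the problem.

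The change is to wording only: no additional patients, visits or data. Power at the planned 6.0 (SD 2.0) stays above 99.9%. The sponsor gives up using a secondary endpoint alone as grounds to progress.
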